## Abstract

**Background::**

Chemotherapy-induced nausea and vomiting is a common problem in patients undergoing chemotherapy, influencing quality of life (QoL) and daily activities. This study will investigate whether therapists’ positive communication may strengthen positive treatment expectations and induce antiemetic effects during antiemetic treatment using standard care, sham acupuncture, or verum acupuncture, compared to neutral communication. It will also investigate whether a variety of patient, therapist and treatment components modify the treatment outcomes.

**Methods::**

This is a trial protocol for a randomized, sham-controlled, patient- and evaluator-blinded clinical trial. Patients (n = 198 patients according to a sample size calculation) with breast, colorectal, or bladder cancer undergoing neo-/adjuvant moderately to highly emetogenic chemotherapy are being randomized in 2 × 3 factorial design to the following conditions: 1. neutral or 2. positive communication style regarding expected treatment effects, during the antiemetic treatment types: A) standard care only (including antiemetics, no acupuncture), or, in addition to standard care, B) sham acupuncture with telescopic non-penetrating needles, or C) verum, penetrating acupuncture. The 2 communication styles 1 and 2 are carried out during the antiemetic treatments given by an intervention therapist immediately pre and post (20 minutes × 2) an intravenous chemotherapy session. Data are being collected at baseline on the day before the chemotherapy session, daily for 10 days, at a 10-day follow-up, and at a follow-up after completing the entire chemotherapy period, lasting about 6 months. Primary outcome is mean score Visual Analog Scale nausea grading for the first 5 days of the chemotherapy session period. Secondary outcomes are for example, vomiting, treatment expectations, QoL, daily and physical activity, and physiological measures. Treatment effect modifiers will be analyzed, for example, blinding success, treatment expectations, and previous nausea experiences.

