The main study hypothesis is that positive communication plus acupuncture (penetrating verum or non-penetrating sham acupuncture) is more effective than neutral communication plus standard care for nausea, calculated as the mean score for the first 5 days of the studied chemotherapy session period. We hypothesize that treatment expectation is a mediator of the effects.

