Self-reported descriptive data: On a baseline questionnaire, patients supply sociodemographic data (eg, sex, age, level of education, profession), clinical data (eg, comorbidities, disease-specific variables, medications), data on previous experience of and belief in acupuncture effects,^
22
^ data on previous nausea experiences in their lives and specifically when undergoing cancer therapy, self-predicted risk for nausea,^
36
^ and data regarding therapeutic alliance, for example, to which extent the patient trusts the therapist to be able to help him/her.^
61
^

Data on nausea and vomiting: Patients complete a measure of nausea and vomiting^
7
^ daily for 10 days, answering questions about the primary outcome (nausea intensity) and the secondary outcomes (nausea occurrence, duration of nausea, vomiting episodes, and consumption of antiemetics). This measure asks the following questions with reference to the past 24 hours: “Have you experienced nausea?” (“No” / “Yes”); “How intense was the nausea?” A 100 mm VAS with verbal anchors “No nausea” and “Worst possible nausea” is used. The accumulated duration (in minutes) of nausea within the past 24 hours is registered. Patients also respond to the questions: “Have you vomited?” (“No”/“Yes”), “How many episodes?” (number of episodes is given), and “Have you consumed rescue antiemetics?” (“No”/“Yes”). They are asked to: “Please detail agent, dose and frequency of each antiemetic agent used.” Also, other kinds of nausea and vomiting-related care consumption is self-registered. Burden is asked for and registered on 2 separate 100-mm VAS: “Did the nausea negatively affect your daily life?.” The same question is posed regarding vomiting, both anchored with 0 (“Not affected at all”) and “100” (“Affected in the worst possible way”; Figure 2).

Expectations data: Patients rate their treatment expectations daily for 10 days, using a valid expectancy measure,^
56
^ “Do you believe that the treatment you are going to receive is effective for nausea and vomiting?” This is measured using a 100 mm VAS anchored with 0 (“I don’t believe at all that it’s effective”) and 100 (“I completely believe that it’s effective”). Post-treatment, the question is written with the modified verb tenses “received” and “was.”

Treatment satisfaction data: On day 10 after the intervention, patients rate their interest in receiving future acupuncture treatment by answering the questions^
37

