The analyzer at the laboratory of each hospital at the study sites analyzes the samples using an enzyme immunoassay kit (Salimetrics LLC, USA). Regarding the precision of the measurements, the total coefficient of variation is 13.3% at 3.4 nmol/L and 6.3% at 29.4 nmol/L. The detection limit is 0.3 nmol/L. If the analyses cannot be done consecutively, the laboratory may store the samples at −20°C for up to 9 months.^
71
^ In the event of storage, the samples will be thawed at room temperature and centrifuged at 1500*g* before assay.

Treatment adherence, complications, and blinding data: At every treatment session, the intervention therapists register their adherence to the study protocol (eg, treated acupuncture points, number of needle stimulations, delivered verbal phrases). The intervention therapists register potential negative side-effects or complications occurring during the treatment sessions.

At the 10-day follow-up measure, patients respond in a binary fashion to a blinding measure^
59
^: “Do you think you have been treated with needles that have penetrated your skin, or do you think the needles have only been placed against the surface of your skin?” They also grade how certain they feel on the accuracy of their response: “Not sure at all, just guessed,” “fairly sure,” “entirely sure.” If patients have received standard care only, they choose the additional alternative “Not applicable, I did not receive any acupuncture treatment.” They respond to the question^
51
^: “During your chemotherapy session, you met an intervention therapist. Do you think you have received treatment from a therapist who emphasized the expected positive effects or one who did not?” This is measured using a 100 mm VAS anchored with 0, “Communicated very negative” and 100, “Communicated completely positive.” Patients in treatment type B-C grade their self-perceived needle-induced pain (“No/little/moderate/very painful”) and register potential side-effects of the acupuncture treatment.

Co-occurring symptoms, consumption of co-interventions: Patients repeatedly grade experience of co-occurring symptoms/problems, fatigue,^
72
^ sleeping quality,^
73
^ anxious and depressed mood,^
74
^ relaxation,^
51
^ pain and unpleasant symptoms (ie, neuropathy symptoms),^
75
^ wellbeing,^
37
^ eating capacity,^
76
^ and stool frequency.^
57

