### Data Analysis Plan

The intention-to-treat principle will be applied when analyzing the study data, that is, all patients will be analyzed as randomized, regardless of whether they complete the study procedure as planned. The primary parameters of interests are the 2 factorial effects (2 main effect, ie, 1. communication style, and 2. treatment type, and one interaction, ie, treatment expectations) during the first 5 days of the studied chemotherapy session period. The evaluator will use a generalized linear mixed effects model (GLMM) to determine if the independent variables communication style and treatment type affect the dependent variable nausea. We take the stratified randomization into account (adjusting for random effects of department on the outcomes) and include baseline characteristics in the analysis model to increase the precision of the estimates.^
77
^ In secondary GLMMs, we will study the effects of the variety of independent variables on vomiting, QoL, and daily and physical activity. Patients who cease to participate (dropouts) and missing data will be handled according to routines as follows. In the main analysis, missing data will be handled using multiple imputations by chained equation.^
78
^ We will specify the multiple imputation model (the choice of auxiliary variables) after comparing patient characteristics between those with complete and those with incomplete data. Under the assumption that data are missing at random, an analysis based on multiple imputation conforms with the intention to treat. We will then also estimate the factorial effects using complete data only. We will conduct a sensitivity analysis by comparing estimates regarding the 2 main effects described above with estimates based on complete data only, in other words, a pattern-mixture model and tipping point analyses. Statistical significance will be defined as a 2-tailed *P* < .05, and the analyses will be performed in IBM SPSS statistics (IBM Corp, Armonk NY, USA).

In line with previous recommendations regarding cost-effectiveness analysis alongside clinical trials, we will specify the methods for cost effectiveness analysis after evaluating these outcomes. If the present evaluation shows significant health benefits on the primary outcome measure, or in at least on 1 secondary outcome, a cost-effectiveness analysis of our intervention will be conducted using a model-based approach.^
79
^

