^ the next natural step will be to present the current large-scale, well-designed study, addressing what constitutes optimal communication for obtaining effects on nausea and vomiting and for improving QoL and capacity in daily and physical activities among patients undergoing chemotherapy. The patients participate in the study during one chemotherapy session, and thus the primary outcome is based on data collected within that session. To intervene with the patients and thus collect data during the entire chemotherapy period for about 6 months was valued to be unethical. We want to minimize the burden of the study on this rather frail patient group until we become aware of the efficacy of the treatment types and the communication styles. If positive communication added to antiemetic treatment is effective, this integrative cancer therapy intervention may be implemented during the entire chemotherapy period. The underlying mechanisms of nausea and vomiting are complex and involve a wide range of biopsychosocial mechanisms.^
35
^ To identify potential *psychological* mechanisms mediating beneficial effects of antiemetic acupuncture, treatment expectations will be analyzed. To identify potential *biological* mechanisms underlying beneficial effects of antiemetic acupuncture, the stress indicators blood pressure, heart rate and cortisol concentration in saliva will be analyzed. The data collection procedures thoroughly collect data on previous nausea experiences, since exposure to emetogenic situations and to previous nausea increases the risk for developing nausea.^2,4,36^

The research team involving and surrounding the authors includes experts in integrative medicine, nursing, physiotherapy, psychology and behavioral medicine, oncology, cell biology, and health economy, thus enabling a broad-based approach to gain new knowledge. The study will contribute knowledge that can be used when treating patients in clinical practice by evaluating the role of healthcare personnel’s communication and patients’ treatment expectations, as well as the use of different antiemetic strategies, that is, using antiemetics alone or antiemetics plus acupuncture. Evaluating the effects of communication and antiemetic therapy as well as identifying moderating and mediating variables on our outcome—nausea—may be expected to be beneficial on at least 3 levels. Individual gains of reduced nausea may include improved self-perceived QoL,^6

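### Blinding success is listed as a treatment effect modifier, but the needle guess is asked only on day 10, after the day 1–5 nausea outcome is complete, so nausea itself can create the interaction

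*Protocol article*

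**What the plan says.** **Outcome window.** Abstract, Methods: "Primary outcome is mean score Visual Analog Scale nausea grading for the first 5 days of the chemotherapy session period". The Sample Size section defines these days as the chemotherapy day and the four that follow.

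**Blinding.** The same abstract paragraph states: "Treatment effect modifiers will be analyzed, for example, blinding success, treatment expectations, and previous nausea experiences". The Data Collection section, under treatment adherence, complications and blinding, gives the timing: "At the 10-day follow-up measure, patients respond in a binary fashion to a blinding measure". A certainty grading and a 100 mm rating of how positively the therapist communicated are described alongside it. No earlier needle guess is described.

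**Expectations.** Patients rate these daily for 10 days. The item is quoted in the future tense, and then: "Post-treatment, the question is written with the modified verb tenses" changed, so that it asks whether the treatment received was effective. The article gives this variable several roles:
- modifier (abstract);
- secondary outcome (abstract: "Secondary outcomes are for example, vomiting, treatment expectations, QoL, daily and physical activity, and physiological measures");
- mediator (end of Introduction: "We hypothesize that treatment expectation is a mediator of the effects");
- a parameter of the primary analysis (Data Analysis Plan: "one interaction, ie, treatment expectations");
- evidence on psychological mechanism (Discussion: "mechanisms mediating beneficial effects of antiemetic acupuncture, treatment expectations will be analyzed").

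**The concern.** An effect modifier should be fixed before treatment can influence it. A guess made on day 10 follows both randomisation and the complete primary outcome. Splitting verum and sham patients by whether they guessed correctly therefore splits them partly by how nauseous they were. The plan could then report that verum acupuncture works in patients who recognised their needles, or that unblinding explains the result, when neither is true. No later modelling choice repairs this for blinding, because the article describes no earlier guess.

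A related risk concerns expectations. Once treatment has been given, the item asks about perceived efficacy on the same days that nausea is reported. If such a rating served as modifier or mediator, less nausea leading to a better rating could be read as expectation leading to less nausea. The Introduction itself concedes that how expectations and symptoms influence each other over time is unknown.

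**Working it through.** **1. Timing.** The outcome covers days 1–5 and the needle guess is asked at day 10. The guess therefore comes about five days after the outcome is complete, whatever model is used.

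**2. SD.** The article states none. Its inputs are a 10 mm difference, 99 per communication group, two-sided alpha 0.05 and power 80%. These imply SD = 10 × √(99/2) / (1.960 + 0.842) = 25.1 mm. An assumed SD of 25 mm reproduces 99 per group, or 198 in total, and is used below.

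**3. Spurious blinding interaction.** Assumptions: no verum effect; 66 patients per acupuncture arm (198/3); the log-odds of guessing penetrating needles fall by 0.4 per SD of nausea, equally in both arms.
- Let d be mean nausea in patients guessing penetrating minus mean nausea in those guessing surface contact.
- A penetrating guess is correct in the verum arm and incorrect in the sham arm. The interaction is (verum correct − verum incorrect) − (sham correct − sham incorrect) = d − (−d) = 2d.
- With half the patients guessing penetrating, numerical integration gives a mean of −0.193 SD among them and +0.193 SD among the others. So d = 2 × (−0.193) × 25 = −9.6 mm, and 2d ≈ −19 mm.
- Verum therefore looks about 9.6 mm better than sham among correct guessers and about 9.6 mm worse among incorrect guessers, although it does nothing.
- Residual SD = 25 × √(1 − 0.193²) = 24.5 mm. With four cells of 33, SE = 24.5 × √(4/33) = 8.5 mm, so the ratio is about 2.26 and the test rejects in about 61% of trials.
- If about 70% guess penetrating (cells of 46 and 20 in each arm), SE = 24.5 × √(2/46 + 2/20) = 9.3 mm and the test rejects in about 53–54%.
- Simulation agrees: about 19 mm, with rejection of 61% at an even split, 59% at 60% and 53% at 70%. About 55% is a fair central figure. With no dependence on nausea, rejection is about 5%.

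Sensitivity to the strength of dependence, with correct-guess coding and an even split (simulated):

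| Log-odds per mm | Per SD of 25 mm | Interaction (mm) | Null trials significant |
|---|---|---|---|
| 0 | 0 | 0 | 6% |
| 0.01 | 0.25 | 12 | 29% |
| 0.02 | 0.5 | 24 | 79% |
| 0.04 | 1.0 | 41 | 100% |

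**4. Expectation rating as mediator or covariate.** Assumptions: 198 patients; communication lowers nausea by 10 mm directly; expectation has no effect on nausea; the later rating falls by 0.25, 0.5 or 0.75 mm per mm of nausea (rating SD 25 mm before nausea, added noise SD 10 mm).
- The apparent indirect effect is −0.5, −1.9 or −3.4 mm, jointly significant in 6%, 21% or 40% of trials. For a rating made before nausea it is under 1%.
- With the later rating as a covariate in the nausea model, the communication effect shrinks from −10 mm to −9.3, −8.3 or −6.9 mm. This is why it matters which rating is meant by the interaction term in the Data Analysis Plan.

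**The case against.** **Expectations.** A reader might infer that expectation ratings cannot serve as modifier or mediator at all, or that the mechanistic results will be produced by the outcome. The article does not support that. The future-tense item implies a rating before treatment, and allocation reaches the therapist only on the intervention day, so a valid pre-allocation modifier may well exist. No section says that past-tense, same-day ratings will be the mediator. Daily ratings allow an early or lagged analysis, and the timeline figures, which might show a rating taken right after the intervention, are not visible here. Which rating enters which model is commonly left to an analysis plan. This objection stands and reduces the expectation part to a risk left open.

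**Role of blinding.** The Discussion ties mechanism to expectations, blood pressure, heart rate and cortisol, not to blinding, which appears as one example in an abstract list. That limits the stakes but does not make the listed analysis valid.

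**Fragility of the size.** With the raw guess as covariate and equal dependence in both arms, the spurious interaction is zero. It returns if dependence differs by arm: about 10 mm if only sham guesses vary with nausea at 0.4 per SD. The abstract, however, names blinding success, which points to correct versus incorrect coding, and there equal dependence is enough.

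**Moving the items.** One might ask for the perceived-communication item straight after the second treatment. Recruitment of Patients shows that the content of the communication styles is deliberately withheld. Asking then would direct patients to the manipulation before they rate most of their nausea. This objection stands, and the item is better left at day 10.

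**Conclusion.** The point holds for blinding success: the plan names as a modifier a variable that it measures only after the primary outcome is complete. With SD 25 mm, correct-guess coding and a log-odds slope of −0.4 per SD in both arms, a null verum effect yields an interaction of about 19 mm, significant in about 55% of trials. The slope is an assumption. The article gives no information on it, and the size runs from nothing to 41 mm over the range shown.

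For expectations the conclusion is narrower. The article leaves open the use of post-treatment, past-tense ratings as modifier, mediator or primary-model term, and does not commit to it.

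A reader might also infer that the main trial result is compromised. It is not: the randomised comparisons of communication style and treatment type are unaffected unless a post-treatment rating enters the primary model.

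**What to change.** - Remove blinding success from the effect modifiers. Report the day-10 needle guess descriptively by arm, with its certainty grading.
- Limit modifiers to variables measured before allocation is revealed, such as the pre-treatment future-tense expectation rating and previous nausea.
- For mediation, name the earliest rating after the communication as the mediator, with later nausea as the outcome (or a lagged analysis), adjusted for the pre-treatment rating.
- Label later past-tense ratings as perceived benefit, not as evidence that expectation reduced nausea.
- State in the Data Analysis Plan that no post-treatment expectation rating enters the primary model as the interaction.
- Keep the perceived-communication item at day 10.

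**Cost.** These are wording changes to the analysis; no data collection changes, and patients already treated remain usable. The price is that blinding can no longer be tested as a modifier and that the mediation claim rests on fewer ratings.

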**Conclusions::**

This trial will expand integrative cancer care’s understanding of the effects of communication for strengthening treatment expectations and thus alleviating chemotherapy-induced nausea and vomiting. If proven effective, the communication model of strengthening positive treatment expectations in patients with risk for nausea and vomiting can be implemented in routine clinical care as part of side-effect management for patients with cancer.

Trial registration: US National Institutes of Health, https://clinicaltrials.gov/study/NCT03232541?term=NCT03232541&rank=1), # NCT03232541.

## Introduction

Despite modern antiemetic treatment,^1
[Bibr bibr2-15347354251361464][Bibr bibr3-15347354251361464]-4^ nausea and vomiting are still considered one of the worst side effects of chemotherapy.^
5
^ These side effects often worsen patients’ quality of life (QoL),^6
[Bibr bibr7-15347354251361464][Bibr bibr8-15347354251361464]-9^ impair daily activities,^7,9,10^ and generate substantial healthcare costs,^
11
^ as well as financial burdens for patients, families, and society as a whole.^
12
^

Approximately 50 to 80 percent of patients experience nausea and/or vomiting during each chemotherapy cycle.^1,13^ These side effects usually occur within 1 to 5 days and can continue up to around 10 days.^1,2^ Although antiemetics play a crucial role in effective nausea and vomiting control,^
14
^ some patients receive inadequate treatment.^3,5,15^ Some patients even decline antiemetic prophylaxis.^
16
^ Without prophylactic medications, moderately emetogenic chemotherapy is associated with nausea and vomiting in 30% to 90% of patients. When using highly emetogenic chemotherapy, nearly all patients experience nausea and vomiting in the absence of adequate prophylaxis.^
17
^

Many patients request non-pharmacological treatments during cancer therapy: More than a fourth of 755 patients undergoing cancer therapy used complementary and alternative medicine (CAM) after receiving their cancer diagnosis.^
18
^ Acupuncture is the most frequently offered complementary treatment within established cancer care in Western countries,^19,20^ and on the top 3 worldwide.^
21
^ Patients report great interest in receiving acupuncture for side effects during their cancer therapy^
22
^ and cancer care personnel highly believe acupuncture to be effective for various cancer-therapy induced side-effects.^
23
^ Guidelines^24,25^ recommend acupuncture to the target population. Despite great interest in acupuncture among patients and personnel^22,23^ and widespread implementation across oncology clinics,^19
[Bibr bibr20-15347354251361464]-21^ there is still limited scientific evidence^25,26^ concerning the method’s specific effects. Few studies have been designed to distinguish *specific effects*, resulting from skin penetration and needle stimulation, from effects of *nonspecific* treatment components, such as treatment expectations and communication during treatment,^
27
^ by adopting a credible sham-controlled design. These studies have presented contradictory results regarding nausea and vomiting outcomes: both positive results^
28
^ and negative results have been observed.^
29
^ Other recent studies have unfortunately not applied any control treatment,^30,31^ or used verum acupuncture as a control treatment, the only difference being that the needles were inserted at non-traditional acupuncture points.^
32
^ Hypotheses, yet unconfirmed by scientific studies,^
33
^ have been proposed stating that acupuncture may have specific effects against nausea and vomiting by inhibiting impulses from the vagus nerve to the vomiting center or by increasing patients’ cortisol concentration.^
34
^ Elevated cortisol concentration may plausibly prevent nausea, potentially through the same mechanisms that corticosteroids (converted to cortisol in the body) do.^
1
^

The underlying mechanisms of chemotherapy-induced nausea involve both biological and psychosocial mechanisms.^
35
^ The risk of nausea is elevated in anxious^2,4^ or hopeless patients^
36
^ and in patients who believe they are at high risk of experiencing nausea,^36
[Bibr bibr37-15347354251361464]-38^ for example, based on previous nausea experiences.^
36
^ Treatment expectation^
37
^ has the potential to modify effects of integrative cancer therapies, acupuncture included. However, acupuncture studies often fail to measure treatment expectations.^
39
^ Responders to acupuncture described themselves to have a more trustful relationship to their therapist than did non-responders.^
40
^ Patients described expectations to be important for shaping new experiences of nausea during chemotherapy.^
9
^ This gives a hypothetical basis for potential antiemetic effects of adopting the non-specific treatment component communication to strengthen positive expectations concerning the effects of a treatment,^41,42^ that is, antiemetic treatment. Non-clinical experimental studies have observed expectancy-related effects on nausea, also in stressful conditions.^
43
^ However, how patients’ expectations and symptom experience influence each other over time is still unknown, raising a question of whether personnel can strengthen patients’ positive expectations through their communication and thus prevent or alleviate symptoms in standard care settings.^39,41,44
[Bibr bibr45-15347354251361464]-46^ A previous study observed a dramatic effect of sham acupuncture in a non-cancer population with bowel health symptoms, especially when given by therapists employing empathic, confidence-instilling communication during treatments.^
47
^ Inspired by that study,^
47
^ we have developed a communication model, involving verbal communication with corresponding non-verbal communication^48,49,50^ intended to strengthen positive treatment expectations. We evaluated the model’s validity in non-cancer individuals. The individuals who had the best effect, were those who, owing to the therapist’s communication, managed to increase their treatment expectations the most.^
51
^

Previous findings^27,47,51^ have shown that acupuncture treatment and non-specific components of the caring situation have great potential to produce valuable effects; these findings need to be evaluated in a scientific study that employs good methodology. Converging observations from previous studies^39,41,44
[Bibr bibr45-15347354251361464]-46^ have suggested that non-specific treatment components can be explored and used systematically, and that this may benefit patients significantly. There is a lack of knowledge regarding if strengthening treatment expectations is effective in clinical contexts.^39,44
[Bibr bibr45-15347354251361464]-46^ More knowledge is also needed about health economic benefits of antiemetic acupuncture^
30
^ and interventions based on non-specific treatment components.^
52
^

In the present protocol, we describe a randomized, sham-controlled, patient- and evaluator-blinded trial to examine the efficacy of a communication model intended to strengthen positive treatment expectations among patients during antiemetic treatment for chemotherapy-induced nausea and vomiting. The twofold objective is to study whether nausea and vomiting, QoL, and daily and physical activities differ between patients with cancer who, during a chemotherapy, receive:

1. Neutral or 2. positive communication about the expected antiemetic effects while undergoing:A. Standard care with antiemetics only, or, added to standard care, B. sham acupuncture, or C, verum acupuncture.

The main study hypothesis is that positive communication plus acupuncture (penetrating verum or non-penetrating sham acupuncture) is more effective than neutral communication plus standard care for nausea, calculated as the mean score for the first 5 days of the studied chemotherapy session period. We hypothesize that treatment expectation is a mediator of the effects.

